### Sample size

Adults in the working population aged between 35 and 66 years will be recruited at all three sites. In a pilot study [8], our group was able to measure an improvement in function with the Disabilities of the Arm, Shoulder and Hand Outcome Measure (DASH) score (median 47 [mean 46 ± 20 SD] to median 34 [mean 32 ± 15 SD]). As a result of a power analysis based on these results, 26 patients per group will be required to achieve 80% power at a significance level of α = 0.05. With an expected drop-out rate of 10%, a total of 60 patients should be recruited, comprising 20 patients at each of the 3 sites.

Inclusion criteria for both groups will be surgical treatment of the shoulder joint after upper arm fracture classified as AO Foundation/Association for the Study of Internal Fixation (Arbeitsgemeinschaft Osteosynthese; AO) type 11 [10]. Participants will be included between the fourth and seventh weeks after surgery. The participant population will be stratified by fracture location (subcapital/capital) and handedness.

Exclusion criteria will be determined during baseline assessment. Participants with limited cognition as defined by a score < 10 points on the Short Orientation-Memory-Concentration Test (SOMC), inadequate level of pain during movement of the affected shoulder joint (pain score > 5 on a pain visual analogue scale [VAS]), strongly limited vision or hearing, heart failure (New York Heart Association stage III-IV), chronic obstructive pulmonary disease with Global Initiative for Chronic Obstructive Lung Disease (GOLD) stage III-IV, walking speed < 0.8 m/second, isolated tuberculum majus fracture of the humerus (AO 11, A1), or fractures with involvement of the glenoid cavity, as well as double fractures or injury of the plexus or the axillary nerve, will be excluded. All participants will give their written informed consent to the study administrators at each centre prior to the clinical baseline assessment.

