**Fig. 1 Fig1:**
[figure not shown]
Plan of assessment and intervention procedures. *DASH* Disabilities of the Arm, Shoulder and Hand Outcome Measure, *ROM* Range of motion, *WMFT-O* Wolf Motor Function Test–Orthopaedic version

Clinical data such as sex, age, body mass index, handedness, date and type of fracture, and date of surgical treatment will be recorded. Furthermore, the participant’s occupation before and after the accident as well as the number of days between the accident and the return to work will be recorded. If the participant will not be able to return to work after the accident, the reason for being incapacitated will be assessed.

The SOMC is an assessment of cognitive impairment and will be applied in this study. It can differentiate between mild, moderate and severe cognitive deficits. The SOMC was derived from the longer Blessed scale [11] to enable it to be performed by a non-physician. The SOMC score highly correlates (*r* = 0.92) with the full scale and is nearly as sensitive as the longer version. Any error score of 0–6 is within normal cognitive limits [12].

In this study the potential pain score in the shoulder during motion will be assessed by the patient and then documented by the therapist as a numerical value. Therefore, a VAS will be used, which was proven to be a valid method for determining pain in clinical routine [13]. As an assessment of overall motor function, the comfortable gait speed over a distance of 10 m will be assessed. The walking course will consist of a total of 14 m, 2 m for acceleration, 10 m for the speed measurement and 2 m for slowing down and stopping. The participants will be directed to walk at their own comfortable pace [14].

The flexibility (range of motion [ROM]) of the shoulder is measured using a goniometer according to the AO neutral-0 method in pain-free range. The maximum angle in elevation, retroversion, abduction and adduction as well as external rotation will be measured. The maximal grip strength will be assessed three times for both hands using a dynamometer (JAMAR Technologies/MSD, Londerzeel, Belgium) according to the American Society of Hand Therapists [15] guideline. The average of three measurements will be calculated for both hands.

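### The cognitive exclusion (SOMC score below 10) runs against the error scale the protocol describes: as written it excludes every cognitively normal patient and admits only those outside the normal range

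*Protocol article*

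**What the plan says.** Two places in the protocol article bear on this point.

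- **Sample size (exclusion criteria).** Those to be excluded include "Participants with limited cognition as defined by a score < 10 points on the Short Orientation-Memory-Concentration Test (SOMC"). The timing is also given: "Exclusion criteria will be determined during baseline assessment". The rule is therefore an operational one, applied by site staff.
- **Clinical assessment (text after Fig. 1).** The instrument is introduced with "The SOMC is an assessment of cognitive impairment and will be applied in this study". Its grading is described: "It can differentiate between mild, moderate and severe cognitive deficits". Its normal range is then given: "Any error score of 0–6 is within normal cognitive limits".

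No other part of the article describes SOMC scoring, mentions a reversed version or gives the maximum of the scale. The SOMC cut-off is the only cognitive eligibility criterion.

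**The concern.** The exclusion criterion reads a low score as impairment, whereas the description of the instrument reads a low score as normal. A site that follows both literally would turn away the patients the trial wants and take those it means to leave out.

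Cognition matters for this design. The primary outcome is the 30-item DASH, which the Discussion describes as self-completed and which is collected by post at 3, 6 and 12 months. The robot training uses game-like exercises with visual and audio feedback. Eligibility is judged at three centres, and the Limitations section already expects difficulty in standardising assessments across them. If the centres resolved the contradiction differently, they would enrol different populations. With 60 patients planned, 20 per site, a few misclassified patients would be noticeable. The published criterion also defines the population to which the result applies.

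**Working it through.** The article offers no figure to reproduce here. The check compares two sets of scores.

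**Inputs**

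- Exclusion set: SOMC score < 10 (Sample size).
- Normal set: error score 0 to 6, so more errors is worse (Clinical assessment).

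**Reading 1: the criterion is on the error scale that the article describes.**

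| Error score | Status under Clinical assessment | Is it < 10? | Result under the exclusion rule |
|---|---|---|---|
| 0, 1, 2, 3, 4, 5, 6 | normal | yes | excluded |
| 7, 8, 9 | outside normal | yes | excluded |
| 10 or more | outside normal, further from it | no | eligible |

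- Normal scores excluded: 7 of 7, or 100%.
- Scores of 10 or more excluded: none.
- Overlap of eligible scores {10 or more} with normal scores {0 to 6}: empty.

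Purely to show that direction is the cause: with the inequality reversed at the same number, none of the scores 0 to 6 would be excluded. This does not mean that 10 is the right threshold.

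**Reading 2: the criterion is on a points-correct scale.**

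Assume points correct = M − errors, where M is the maximum, which the article does not give.

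- Excluding scores < 10 then means excluding patients with M − errors < 10, that is, errors > M − 10.
- The number of errors tolerated is therefore M − 10.
- The rule matches the quoted normal range exactly only if M − 10 = 6, so M = 16. For any larger M, the rule admits M − 16 error scores beyond the normal range; for any smaller M, it excludes some normal scores.

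On this reading the direction is sensible, but how much impairment the trial tolerates depends wholly on a number that is not stated.

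**Comparison.** Reading 1 gives a rule that contradicts its own purpose. Reading 2 gives a workable rule on a scale that the article does not describe, next to a normal range on the opposite scale. The two readings admit different patients, and the text does not settle which applies.

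**The case against.** The strongest reply is that the intent is plain. The criterion names the group to be excluded as people with limited cognition, and it says score where the other section says error score, so a points-correct scoring may well have been meant. In that case the rule is sound and only the description of the instrument is mismatched. Assessments are made by trained assessors, and recruitment had reached 50% among adults aged 35 to 66, which is hard to square with a rule that turned away everyone in the normal range. Eligibility is settled before randomisation, which is blocked within centre, so a misapplied rule would fall on both arms alike and would not bias the comparison. Scoring details may also sit in the full protocol or the cited source.

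Much of this stands. The article gives no evidence that any site applied the literal rule or enrolled impaired patients. The effect would be on the population enrolled, on generalisability and perhaps on the quality of self-report, not on the treatment contrast or the sample size. The 100% figure describes the rule; it does not estimate how many patients were affected.

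The contradiction remains. Clear intent tells staff which kind of patient to exclude but not which scale or cut-off to use. Nor is this an omission explained by condensation: the article states both the cut-off and the scale, and they conflict. A text-conversion fault is unlikely, since the pain and walking-speed limits in the same sentence are intact and run in the expected direction.

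**Conclusion.** The concern holds. On the only SOMC scale the article describes, the criterion excludes all of the normal range (0 to 6 errors) and admits only scores of 10 or more, every one of them outside that range. This rests on reading the two statements on the same scale. If a points-correct scale was meant, the inequality runs the intended way, but the article then describes the opposite scale and the cut-off cannot be interpreted against the normal range it quotes. Either way the eligibility rule cannot be followed reliably as written and must be corrected. Confidence that the two statements conflict is high. What the sites actually did, and which threshold is right, cannot be determined from the article.

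**What to change.** 1. State the scoring direction of the SOMC and its range, and express the exclusion cut-off and the normal range on that same scale in both sections. The exclusion must fall on the impaired end; on the error scale that means excluding above a stated number of errors. The sponsor must supply the threshold.
2. Send a clarification to all three sites and ask each to confirm the direction and cut-off it has been using.
3. Check the SOMC values held in REDCap, for enrolled patients and for any screen failures recorded there, against the intended rule, and report any misclassified patients.

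The cost is a one-line amendment or site clarification plus a short data check. With recruitment at 50%, and taking that against the planned total, the check covers about 0.5 × 60 = 30 enrolled patients, plus the screen failures. The sample size and the analysis need no change.

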### Clinical assessment

The estimated total duration of clinical baseline and follow-up assessments will be 160–180 minutes. The clinical assessment will be carried out for all participants before the first potential training session (baseline) and after the last potential training session (follow-up 1 at 3–5 weeks after baseline). For analysis of sustainability, further postal follow-up assessments (2, 3 and 4) will be carried out 3, 6 and 12 months after the baseline assessment (Fig. 1). In these follow-up assessments, only the DASH and the ability to work (what job to what extent) will be evaluated. All assessments will be performed by trained assessors.

**Fig. 1 Fig1:**
[figure not shown]
Plan of assessment and intervention procedures. *DASH* Disabilities of the Arm, Shoulder and Hand Outcome Measure, *ROM* Range of motion, *WMFT-O* Wolf Motor Function Test–Orthopaedic version

Clinical data such as sex, age, body mass index, handedness, date and type of fracture, and date of surgical treatment will be recorded. Furthermore, the participant’s occupation before and after the accident as well as the number of days between the accident and the return to work will be recorded. If the participant will not be able to return to work after the accident, the reason for being incapacitated will be assessed.

The SOMC is an assessment of cognitive impairment and will be applied in this study. It can differentiate between mild, moderate and severe cognitive deficits. The SOMC was derived from the longer Blessed scale [11] to enable it to be performed by a non-physician. The SOMC score highly correlates (*r* = 0.92) with the full scale and is nearly as sensitive as the longer version. Any error score of 0–6 is within normal cognitive limits [12].

In this study the potential pain score in the shoulder during motion will be assessed by the patient and then documented by the therapist as a numerical value. Therefore, a VAS will be used, which was proven to be a valid method for determining pain in clinical routine [13]. As an assessment of overall motor function, the comfortable gait speed over a distance of 10 m will be assessed. The walking course will consist of a total of 14 m, 2 m for acceleration, 10 m for the speed measurement and 2 m for slowing down and stopping. The participants will be directed to walk at their own comfortable pace [14].

The flexibility (range of motion [ROM]) of the shoulder is measured using a goniometer according to the AO neutral-0 method in pain-free range. The maximum angle in elevation, retroversion, abduction and adduction as well as external rotation will be measured. The maximal grip strength will be assessed three times for both hands using a dynamometer (JAMAR Technologies/MSD, Londerzeel, Belgium) according to the American Society of Hand Therapists [15] guideline. The average of three measurements will be calculated for both hands.

In order to describe the extent to which the participants correctly follow medical advice and the therapy sessions, their adherence will be documented. This will be provided by recording the duration and frequency of additional training that contains conventional occupational and physical therapy (group or individualised) during the intervention.

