### Statistics

The centre and the number of treatment units will be regarded as possible covariates for the primary outcome. All data assessed will be described descriptively (mean, SD, 95% CI and median for metric variables; frequency and percentile for categorical variables). After checking the data for normal distribution by comparing the distribution histograms and Shapiro-Wilk test, the group comparison will be carried out with the *t* test or the rank-based Wilcoxon test. For the primary outcome analysis of covariance with study centre, number of therapy units (to take account of the training inhomogeneity) and injury severity (to take account of the patient’s homogeneity) as covariates will be performed. The secondary outcome (WMFT) will be analysed to generate study hypotheses using the methods described above. Inferential statistics will follow an intention-to-treat approach with mean imputation or regression imputation for all randomised patients with incomplete datasets if deemed necessary. Per-protocol analysis will be performed for evaluation of the efficacy of the intervention in patients with complete datasets and without protocol violations.

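### Days from accident to return to work is undefined for patients who do not return, so the planned mean, SD and median would describe returners only (minor)

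*Protocol article*

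**What the plan says.** All references are to the protocol article.

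- **Variable.** Clinical assessment (text under Fig. 1) states that "the number of days between the accident and the return to work will be recorded".
- **Non-return is foreseen.** The next sentence reads "If the participant will not be able to return to work after the accident, the reason for being incapacitated will be assessed". That yields a reason but no number of days.
- **Work status.** At the postal follow-ups 3, 6 and 12 months after baseline, "only the DASH and the ability to work (what job to what extent) will be evaluated".
- **Summary rule.** Statistics: "All data assessed will be described descriptively (mean, SD, 95% CI and median for metric variables", and "frequency and percentile for categorical variables". No exception is made for a time that the end of follow-up can cut off.
- **Missing data.** Statistics allows "mean imputation or regression imputation for all randomised patients with incomplete datasets", but within inferential statistics and only where judged necessary.
- **Loss to follow-up.** Sample size: "With an expected drop-out rate of 10" per cent.
- **Status of the variable.** DASH is the primary outcome and WMFT-O the secondary. Limitations says that return to work would need a larger sample and was not a purpose of the trial. The Discussion mentions an earlier return as a possible consequence.

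**The concern.** The protocol sets one rule for all metric data and also defines a metric variable that the rule does not fit. A mean, SD, confidence interval or median of days to return can be computed only from patients with a return date. Whether a patient returns within follow-up is decided after randomisation and may depend on treatment, so the returners in the two arms are not comparable groups. An arm that brings more slow recoverers back to work adds long times to its own mean and can look worse for it.

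The stake is a misleading descriptive figure on return to work. Low power makes such a figure imprecise, but that is a separate matter from the bias in it.

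**Working it through.** **Inputs.** The protocol states no figure for return to work, so there is nothing of its own to reproduce. All rates and times below are assumptions. The horizon c is day 365 after the accident unless stated. Two quantities are compared in each arm:

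- returner mean = E[T | T ≤ c], which is what the stated rule produces;
- restricted mean = E[min(T, c)], mean days off work up to c over all patients.

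**1. Benefit consists of extra late returners.** Control: 60% return at day 110, 10% at day 280, 30% not by c. Robot: 60%, 30% and 10%.

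- Returner mean, control: (0.6×110 + 0.1×280)/0.7 = 94/0.7 = 134.3.
- Returner mean, robot: (0.6×110 + 0.3×280)/0.9 = 150/0.9 = 166.7. Robot looks 32.4 days worse.
- Restricted mean, control: 66 + 28 + 0.3×365 = 203.5.
- Restricted mean, robot: 66 + 84 + 0.1×365 = 186.5. Robot is 17.0 days better.
- Median among returners: day 110 in both arms, since 60/70 and 60/90 of returners are at day 110. The median shows no difference rather than a reversal.

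**2. Same timing among those who can return, fewer never-returners.** Times are lognormal with median 150 and log-SD 0.7; never-returners are 30% (control) and 10% (robot).

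- Returner mean: 152.8 in both arms, since the timing is the same.
- Restricted mean of the lognormal part: 174.4.
- All patients, control: 0.7×174.4 + 0.3×365 = 231.6.
- All patients, robot: 0.9×174.4 + 0.1×365 = 193.5. A 38.1-day benefit does not show.

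**3. Uniform speed-up, no never-returners.** With log-median μ and log-SD s, p = Φ((ln c − μ)/s), A = exp(μ + s²/2)·Φ((ln c − μ − s²)/s), returner mean = A/p and restricted mean = A + (1 − p)c.

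| Medians (log-SD) | Not back by c | Returner means | Difference | Restricted means | Difference | Loss |
|---|---|---|---|---|---|---|
| 150 vs 120 (0.7) | 10.2%, 5.6% | 152.8, 132.0 | 20.7 | 174.4, 145.1 | 29.3 | 29% |
| 180 vs 150 (0.8) | 18.8%, 13.3% | 162.9, 148.3 | 14.6 | 201.0, 177.2 | 23.8 | 39% |

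The direction is kept and the size shrinks.

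**4. Does the horizon matter?** Follow-up runs 12 months from baseline, and inclusion is 4 to 7 weeks after surgery. Planned follow-up therefore ends 28 + 365 = 393 to 49 + 365 = 414 days after surgery, and no earlier than that counted from the accident. Repeating the cases at c = 393 and c = 414:

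- Case 1: returner means are unchanged. Restricted means are 94 + 0.3c and 150 + 0.1c, so robot's advantage is 0.2c − 56 = 22.6 and 26.8 days.
- Case 3, medians 150 vs 120: the loss is 27% and 26%.
- Case 3, medians 180 vs 150: the loss is 37% and 36%.

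The longer horizon softens the attenuation slightly and does not remove it.

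**5. Would imputation help?** In case 1, giving non-returners their own arm's mean leaves 134.3 and 166.7 unchanged and understates the SD. Giving them the pooled returner mean, (94 + 150)/1.6 = 152.5, yields 94 + 0.3×152.5 = 139.8 and 150 + 0.1×152.5 = 165.3, still in the wrong order.

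**The case against.** **Non-returners are described elsewhere.** A reader might infer that the arms as a whole are described on returners only. The document does not support that. Ability to work is collected at 3, 6 and 12 months without restriction to returners, reasons for non-return are recorded, and both fall under the frequency rule. A 30% versus 10% gap in non-return would show there. This stands and limits the harm, but it does not correct the days summary itself.

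**Return to work is not a trial outcome.** A reader might infer that an efficacy conclusion is at risk, or that earlier return is the benefit the trial sets out to show. Neither is supported: the Discussion calls it only possible, and Limitations says return to work was not a purpose of the trial. This stands and sets the severity.

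**Imputed return days are not a stated plan.** The imputation clause belongs to inferential statistics and is conditional, and no test of return to work is announced. This stands. Imputation matters only as a remedy that would not work if it were tried.

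**The analysis plan may deal with it.** This is a condensed article and the SAP is not shown. That would answer a complaint of silence. Here, however, a rule is stated for all assessed data, and it does not fit a variable that the same article defines.

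**The size is assumed.** Reversal needs a particular pattern of benefit and a material rate of non-return. This stands; reversal is a possibility, not a prediction.

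**Conclusion.** The point holds as a minor one. Applied as written, the Statistics rule gives a returners-only mean, SD, confidence interval and median for days to return to work. Under assumed rates this reverses a 17-day advantage into an apparent 32-day disadvantage (case 1), conceals a 38-day advantage (case 2), or shrinks a uniform speed-up by about 26% to 39% (case 3, over the three horizons). These are expected values under illustrative distributions. The documents give no return-to-work rates, so none of them forecasts this trial. The DASH conclusion and the WMFT-O analysis are unaffected.

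**What to change.** In Statistics, add a sentence that exempts days to return to work from the mean/SD rule and from any imputation. Report descriptively by arm, for randomised patients who were working at the time of the accident:

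- a Kaplan-Meier curve, or restricted mean days off work, to one common horizon that lies within follow-up (which ends 12 months after baseline);
- beside it, the proportion back at work at 3, 6 and 12 months.

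Censor patients who are lost or not yet back at their last contact. Count permanent incapacity as no return up to the horizon, not as censoring at the date it is recorded. Day 365 after the accident would qualify as a horizon, since planned follow-up reaches at least 393 days after surgery.

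The cost is one sentence and a little more analysis work. No new data, patients or visits are needed.
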